#### Delivery of the intervention

The intervention will be delivered by one or two designated trained nursing officers who have an interest in this new role and are willing to deliver the intervention. The details of the nurses training have been described previously.

### Outcome measures

#### Baseline assessment

Qualitative interviews will be conducted with participants, as described in the “Phase 2—Qualitative study” section below. The following assessments will also be completed among all participants: assessment of level of suicidal intent associated with the recent act of non-fatal self-poisoning (via the Pierce Suicide Intent Scale (PSIS), an internationally used scale for the assessment of suicide intent that has been used previously in Sri Lanka [35]) and presence of depression (via the Patient Health Questionaire-9 (PHQ-9) [36, 37] and Peradeniya Depression Scale (PDS) [38]). The PHQ-9 is a well-recognized tool for the screening of depression and has been validated for use in Sri Lanka, with the cutoff score of 10 or above indicating the presence of depression [38]. The PHQ-9 can also be used to examine the severity of depressive symptoms, with scores of 1–4, 5–9, 10–14, 15–19, and 20–27, indicating minimal, mild, moderate, moderately severe, and severe depressive symptoms, respectively [38]). The PDS is a screening tool for the identification of depression that was developed and validated for use in Sri Lanka, which considers the local cultural idioms of distress [38]. Participants will also be screened for anxiety (via the Generalized Anxiety Disorder 7-item scale (GAD 7)) [39] and psychological distress (via the General Health Questionnaire (GHQ 30)) [40] and assessed for coping strategies (via the Brief Coping Inventory, Brief COPE [41]). As far as possible, scales that have been translated to the local language and validated for use in Sri Lanka will be used. In the case of the GAD 7 and the Brief COPE, no validated versions are available, but these scales will be translated to Sinhala and back-translated and checked for accuracy prior to use. The baseline investigations will be carried out a few days (up to a week) after the act, allowing time for recovery from the immediate distress following the act of non-fatal self-poisoning.

### Follow-up assessments at 6 months (intermediate) and 1 year (final assessment)

Qualitative interviews will be conducted among the participants to explore the acceptability of the counseling intervention, whether the participants perceived it as helpful, particularly with regards to coping with acute emotional distress, and components (if any) of the intervention that they particularly remembered or liked. Details of the qualitative assessments are given below (phase 2). Nurses who delivered the intervention will also be interviewed regarding their attitudes and perceptions towards the acceptability and feasibility of delivering the intervention (further details are provided below, in the “Phase 2—Qualitative study” section).

Additionally, assessment of levels of anxiety, depression, and how the person copes with situations of acute emotional distress will be conducted using the measures described above for the baseline assessment. Further secondary outcomes of interest will be rates of repetition and the presence of suicidal ideation, at 6 months and 1 year follow-up. This will be assessed using a structured interviewer-administered questionnaire.

The follow-up assessments at 6 months and 12 months will occur at the hospitals where the initial recruitment took place. Care will be taken to conduct the 6-month and 1-year assessments in a confidential and sensitive manner, to avoid any further distress. After the final assessment, the participants will be informed that this is the last study assessment, but if relevant, they will be encouraged to continue treatment as usual as instructed by their treating team. If required (if the participants are found to require further psychiatric care during the 6 months and 1 year follow-up), the participants will be linked with and referred to ongoing psychiatric care and follow-up.

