Thus, the primary objective of this study is to explore the acceptability and feasibility of a counseling intervention being delivered by nurses. The secondary objective is to explore the potential efficacy of the intervention for the improvement of skills to cope with situations of acute emotional distress and to reduce rates of anxiety, depression, and future repetition and suicidal ideation. It is anticipated that the findings of this pilot study will help determine and assess the acceptability and feasibility of this counseling intervention, as well as indicate the more useful aspects of this intervention in order to develop it for further exploration in a larger trial. It will also inform other aspects of a future trial, such as the sample size, indicate the level of loss to follow-up, and help assess treatment as usual.

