**Fig. 1 Fig1:**
[figure not shown]
Study flow chart

Primary outcomes will be assessment of feasibility and acceptability of the counseling intervention delivered by nurses. Acceptability and feasibility of this intervention, as experienced by the nurses who deliver the intervention and the participants who receive the intervention, will be assessed qualitatively. The secondary outcome is to explore the potential efficacy of the intervention for the improvement of skills to cope with situations of acute emotional distress and to reduce the rates of anxiety, depression, and future repetition and suicidal ideation.

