#### Randomization procedure

The intervention will be assessed using block randomization technique, in order to reduce bias and achieve balance in the allocation of participants to the intervention and control arm. An allocation sequence will be provided by the off-site statistician (independent of the research team) and will be based on a computer-generated list of random numbers, to allocate patients to the intervention plus TAU or TAU alone.

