### Analysis

A strict intention to treat approach will be followed in the analysis. For missing data with regard to the main outcome, variable imputation will be used. The study and the control groups will be described using descriptive summary statistics (mean, standard deviation, count percent). The effect of the intervention will be assessed with a relative risk of severity of depression and other endpoints such as coping skills, levels of anxiety, depression, alcohol misuse, and repetition of self-harm.

Analyzing the qualitative interviews will be started parallel to the conducting of the interviews. The researcher will read the interview transcripts carefully several times to have a sense of the whole data, identifying emerging themes and categories [45]. She will discuss emerging themes, concepts, and contradictions with other designated investigators in the study. A code book will be created and modified until the final set of codes is obtained and reached to the data saturation point when there is no emergence of further new themes.

Qualitative data analysis will be conducted using a thematic content analysis approach following a systematic process. Codes will be applied to the transcripts and converted into categories to represent the main themes arising from the data [46]. Triangulation of themes and concepts will be used to further compare and contrast the data from the different participating groups. It is anticipated that this will strengthen the reliability and validity of the analysis. The analysis will be conducted in the original Sinhala language, and final themes will be translated into the English language by the researcher in cooperation with a professional translator.

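### Suicidal ideation is a secondary efficacy outcome at 6 months and 1 year, but the listed baseline battery has no designated measure of current ideation

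*Protocol article*

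**What the plan says.** The objectives at the end of the Background include exploring whether the intervention has the potential "to reduce rates of anxiety, depression, and future repetition and suicidal ideation". The paragraph under Fig. 1 in Methods/design repeats this as the secondary outcome: "to reduce the rates of anxiety, depression, and future repetition and suicidal ideation".

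The Baseline assessment section names six instruments for all participants: PSIS, PHQ-9, PDS, GAD 7, GHQ 30 and Brief COPE. The only one concerned with suicidality is the PSIS, described as "assessment of level of suicidal intent associated with the recent act of non-fatal self-poisoning".

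The follow-up section treats two groups of outcomes differently. For the first, "assessment of levels of anxiety, depression, and how the person copes with situations of acute emotional distress will be conducted using the measures described above", meaning the baseline instruments. For the second, "Further secondary outcomes of interest will be rates of repetition and the presence of suicidal ideation, at 6 months and 1 year follow-up". The instrument for the second group is named only there: "This will be assessed using a structured interviewer-administered questionnaire".

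The randomisation section has a concurrent control, with a list "to allocate patients to the intervention plus TAU or TAU alone". The Analysis section says: "The effect of the intervention will be assessed with a relative risk of severity of depression and other endpoints such as coping skills". It also calls for intention to treat, and for imputation of missing data on the main outcome.

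**The concern.** Repetition is an event after entry, so it needs no baseline value in the same sense. Ideation is a state that may already be present at entry. It is the one symptom-type efficacy outcome for which the article assigns a tool at follow-up and none at baseline.

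Three things are at stake.

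- **Description.** A follow-up prevalence cannot show whether ideation is new or has persisted. The pilot is meant to inform a larger trial, including its sample size and expected loss, and ideation at entry is part of what that trial would need.
- **Precision.** Direct adjustment for ideation at entry is not possible.
- **Missing data.** Half the sample may be lost. If loss depends on ideation at entry, and does so differently in the two arms, a comparison of completers is no longer protected by randomisation. Without the entry value this cannot be checked directly, and the value cannot inform imputation.

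**Working it through.** **1. The sections side by side**

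| Outcome | Tool at baseline | Tool at 6 and 12 months |
|---|---|---|
| Depression | PHQ-9, PDS | same |
| Anxiety | GAD 7 | same |
| Coping | Brief COPE | same |
| Suicidal ideation | none designated (PSIS refers to the past act) | structured questionnaire |

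**2. The plan's own figure.** The only stated calculation concerns the PHQ-9: difference 4.7, SD 4.49, two-sided 0.05, 80% power.

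n = 2 × (1.96 + 0.8416)² × 4.49² / 4.7² = 2 × 7.849 × 20.16 / 22.09 = 14.3, so 15 per group.

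With 50% loss, 15 / (1 − 0.50) = 30. Both figures reproduce. (The exact t-test solution is 15.35, with power 0.790 at 15.) The article gives no figure for ideation.

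**3. Evaluable numbers.** The target of 150 can be read as a total (75 per arm) or as per arm. After 50% loss that leaves about 37 or 75 per arm. I therefore used 37, 75 and 150.

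**4. Validity and precision without a baseline value.** The documents give no ideation rates, so these are assumptions: half of participants have ideation at entry; follow-up ideation is 40% in those with it and 10% in those without; the intervention halves both.

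- Control rate: 0.5 × 0.40 + 0.5 × 0.10 = 0.25
- Intervention rate: 0.5 × 0.20 + 0.5 × 0.05 = 0.125
- True difference: 0.125

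In 20,000 simulated trials per setting, the unadjusted test compared the two follow-up proportions. The adjusted test was Mantel-Haenszel, stratified by ideation at entry.

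| Evaluable per arm | Type I error, unadjusted | Mean difference found | Power, unadjusted | Power, adjusted |
|---|---|---|---|---|
| 37 | 0.049 | 0.125 | 0.28 | 0.30 |
| 75 | 0.047 | 0.125 | 0.51 | 0.54 |
| 150 | 0.049 | 0.125 | 0.80 | 0.83 |

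The unadjusted comparison keeps its error rate and is unbiased. The cost of having no baseline value is about 2 to 3 points of power.

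**5. Drop-out.** The simulation has no informative loss, so it does not cover this part. Let q₁ and q₀ be the shares of completers with ideation at entry in the intervention and control arms. With no treatment effect and the risks above, the expected difference at follow-up (control minus intervention) is

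(q₀ − q₁) × (0.40 − 0.10).

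If differential loss opened a gap of 10 points, the comparison would shift by 10 × 0.30 = 3 points. A gap of 16 points would shift it by 4.8. The documents do not indicate how large such a gap would be. Without the entry measure, the trial could not observe it directly either.

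**The case against.** A reader might infer that the trial cannot show a reduction in ideation at all. The documents do not support that. There is a concurrent randomised control, the objective is worded in terms of rates, and the effect measure is a relative risk between arms. A lower rate in the intervention arm at 6 or 12 months is valid evidence with no baseline value. A fall from baseline would not be better evidence: participants enter within about a week of the act, and the article itself says distress abates soon afterwards, so ideation could fall in both arms.

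A reader might also treat chance imbalance at entry as bias. With entry rates assumed at 30% to 50%, the 95% range of the difference between arms, 1.96 × √(2p(1−p)/n), is about ±15 to ±16 points at 75 per arm, ±21 to ±23 at 37, and ±10 to ±11 at 150. These are sampling errors of the entry proportions. Only part carries through to follow-up, and the standard error of the randomised comparison already includes it. They do not count as evidence of bias.

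Other points also limit the concern. PSIS, PHQ-9, PDS and GHQ 30 are partial proxies for ideation at entry. Ideation is a further secondary outcome in a pilot whose primary aims are acceptability and feasibility. The article may condense a fuller baseline form. These reduce the weight of the point but do not remove it: the printed list is specific, and the follow-up section names ideation only after entry. The PHQ-9 cannot be assumed to fill the gap, since the article describes it only as a depression measure and does not give its items.

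**Conclusion.** The point holds as a minor design weakness that is worth correcting. As described, the trial can validly compare ideation between arms at 6 and 12 months. It cannot report change in ideation, distinguish new from persisting ideation, check balance on it, adjust directly for it, or relate loss to follow-up to it.

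The measurable cost is about 2 to 3 points of power at 37 to 150 evaluable per arm, under the assumed rates of 50% at entry and 40% against 10% at follow-up. The drop-out part cannot be sized from the documents. It rests on the 50% loss allowed for in the sample size section, and on the possibility that loss is related to ideation at entry and differs between arms. The imputation planned in the Analysis section is for the main outcome, which the article does not say includes ideation. The argument about imputation therefore applies only if ideation is imputed.

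**What to change.** Ask the same structured ideation question(s) at the baseline interview as at 6 months and 1 year, and add them to the listed baseline battery. Adjust the between-arm comparison of follow-up ideation for the baseline answer. Report loss to follow-up by baseline ideation and arm, and include the answer in any imputation of ideation.

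The cost is one or two extra questions at an interview that already takes place with every participant, and one covariate in the analysis. It has to be done at enrolment, because the entry value cannot be obtained afterwards.

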### Plan of contact for those who do not attend

All participants will be reminded of their follow-up assessment by a telephone call and letter, prior to their scheduled follow-up visit. They will also be offered re-imbursement to cover their travel costs to the hospital. Those who do not attend their follow-up visits (either the intermediate or final evaluation) will be contacted again by telephone, and by letter, and will be encouraged to attend. If the person does not respond to two phone calls and the written reminder, they will be considered lost to follow-up.

#### Sample size

Previous interventional studies have examined for changes in the severity of depression, using the PHQ-9 as an outcome measure [42]. One study reported that patients in the intervention group had significantly fewer depressive symptoms compared with patients in the usual care group at 12 weeks follow-up, and the PHQ-9 mean score at 3 months follow-up was 2.4 and 7.1 in the intervention and control group respectively (4.7 mean difference) [42]. The difference between the groups was significant (*p* < .001) using baseline scores as the covariate. A sample size of 15 in each group gave an 80% power to detect the difference in means of 4.7, assuming that the estimated common standard deviation is 4.49 and using a two-group *t* test with a two-sided significance level of 0.05 [42]. Based on similar calculations and allowing for a 50% drop-out rate, we calculated a minimum of 30 participants in each group; however, since our study will be conducted among those who have attempted self-poisoning, we anticipate (based on previous studies) that a little less than 50% of the sample will be suffering from depression [43]. Furthermore, through this intervention, we are planning to examine for clinically relevant changes of depression levels (PHQ-9 scores above 10, indicating a moderate level of depression or above, rather than in the < 10 range quoted in the previous study). To allow for this greater margin, we plan to recruit a sample of 150 intervention and controls.

### Phase 2—Qualitative study

The qualitative component of this study complements the quantitative component of the study. Using qualitative methods, we will explore the feasibility and acceptability of the newly introduced intervention in a large tertiary care hospital setting, from the point of the nurses as well as those who receive the intervention, and will explore a range of perspectives.

We will conduct qualitative in-depth interviews with the participants during the hospital stay (pre-intervention) and follow-up (post-intervention). This is a central part of the qualitative study as we consider the experiences of nurses who deliver the intervention and participants to be crucial to evaluate the acceptability and feasibility of the counseling intervention. Further, we recognized that the screening instruments using in the quantitative study may not fully capture the complex interplay of factors that may contribute towards the act of self-poisoning. The qualitative component of the study will help explore the social and cultural aspects related to non-fatal self-poisoning which could be effective to develop future interventions to reduce non-fatal self-poisoning in Sri Lanka. These interviews will be also conducted with a view of the triangulation of qualitative and quantitative data.

### Interviews with nurses who deliver the intervention

In-depth interviews will be conducted with the two designated trained nurses who voluntarily engaged to delivered the intervention, soon after the completion of the intervention period (of the RCT), to explore feasibility and acceptability of the intervention, as perceived by the nursing officers. The interviews will allow them to share stories and challenges broadly in an open approach. The nurses’ overall experiences regarding their new role of counseling persons who have attempted self-poisoning will be explored. This will include their perceptions of the experiences of delivering the intervention—whether they thought the training was adequate—use of the manual, what skills they think are needed for being an effective counselor, impact of age or service experiences of nurses on delivering the intervention, and challenges they faced and their suggestions for further improving the process. This will be conducted allowing the maintenance of an open approach so that the participants can bring in their own perspectives.

#### Interviews with study participants

Similarly, qualitative interviews will be conducted among the study participants who received counseling from the nurses, as well as those who did not receive the counseling intervention, during the hospital stay and at 6 months follow-up. Exploring perceptions, experiences, and attitudes of the participants about the counseling they received from the nurses is the key in order to explore the acceptability of the intervention from the recipients’ point of view. We will also explore their attitudes and perception towards the counseling intervention they received and whether they found it helpful or unhelpful with regards to coping with situations of emotional distress. These interviews will also explore the characteristics of nurses as counselors that participants identify as supportive or unsupportive and to see whether this can be taken into consideration to the further improvement of the intervention.

We will also explore participant experiences after the act; the factors or reasons for the act as perceived by the participants and their family reaction towards the act. Further interviews will also be used to explore the way participants perceive how they cope with situations of acute emotional distress pre- and post-intervention.

The interviews will be semi-structured, guided with a theme list to cover all relevant issues during the interview, and will be conducted in Sinhala in a culturally sensitive manner. It is anticipated that the interviews will encourage participants to share sensitive issues and stories relating to the self-poisoning incident.

Participants will be selected following maximum variation sampling strategy technique [44], representing different age groups, employment groups, ethnic groups, and rural/ urban origin for the interviews, and interviews will be conducted until data saturates.

### Data management

Data collection and accurate documentation will be the responsibility of the study staff under the supervision of the principal investigator. The principal investigator, other investigators, and research coordinator will be the involved research staff in this study. All source documents will be reviewed by the study team and data entry staff who will ensure that they are accurate and complete. All interviews and focus group discussion will be audio recorded and transcribed in the original Sinhala language by the researcher. All the data and transcriptions will be kept strictly confidential and only referred to by the researcher.

### Analysis

A strict intention to treat approach will be followed in the analysis. For missing data with regard to the main outcome, variable imputation will be used. The study and the control groups will be described using descriptive summary statistics (mean, standard deviation, count percent). The effect of the intervention will be assessed with a relative risk of severity of depression and other endpoints such as coping skills, levels of anxiety, depression, alcohol misuse, and repetition of self-harm.

Analyzing the qualitative interviews will be started parallel to the conducting of the interviews. The researcher will read the interview transcripts carefully several times to have a sense of the whole data, identifying emerging themes and categories [45]. She will discuss emerging themes, concepts, and contradictions with other designated investigators in the study. A code book will be created and modified until the final set of codes is obtained and reached to the data saturation point when there is no emergence of further new themes.

Qualitative data analysis will be conducted using a thematic content analysis approach following a systematic process. Codes will be applied to the transcripts and converted into categories to represent the main themes arising from the data [46]. Triangulation of themes and concepts will be used to further compare and contrast the data from the different participating groups. It is anticipated that this will strengthen the reliability and validity of the analysis. The analysis will be conducted in the original Sinhala language, and final themes will be translated into the English language by the researcher in cooperation with a professional translator.

